### Medication Dosing for Each Group:

#### Varenicline Adaptive Treatment Arm (n=75)

Participants who chose Varenicline-based treatment and are then randomized to the Varenicline Adaptive Treatment Arm will receive the following:

4 weeks prior to TQD: Begin Varenicline with this schedule:

Day 1-3: 0.5 mg q AM for 3 days (with placebo Varenicline in the evening)

Day 4-7: 0.5 mg BID

Day 8 to end of treatment: 1 mg BID

This group will remain on 1 mg BID Varenicline x 3 weeks pre-TQD, then 12 weeks post TQD.

At the 2 week pre-TQD visit, this group will be assessed for “Response” to Pre-quit Varenicline:

**a. Varenicline Non-Responders:** Participants who do NOT show > 50% reduction in cigarettes-per-day from baseline will be continued on Varenicline, and Bupropion will be added as a “rescue medication.”

Bupropion will be added to their regimen 1 week prior to the TQD with this schedule:

Day 1-3: 150 mg q AM

Day 4 to end of treatment: 150 mg BID

Bupropion will be continued for 12 weeks post TQD.

**b. Varenicline Responders:** Participants who show > 50% reduction in cigarettes per day from baseline will be continued on Varenicline as their only active medication.

1 week prior to the TQD, Placebo Bupropion will be added with this schedule:

Day 1-3: 1 placebo pill q AM

Day 4 to end of treatment: 1 placebo pill BID

Placebo Bupropion will be continued for 12 weeks post TQD.

#### **Varenicline Standard Treatment Arm (n=75)**

Participants who chose Varenicline-based treatment and are then randomized to the Varenicline Standard Treatment Arm will receive the following:

4 weeks prior to TQD: start Placebo-Varenicline 1 pill BID

1 week prior to TQD: stop placebo Varenicline and start real Varenicline on the following start up schedule:

Day 1-3: 0.5 mg q AM for 3 days (with placebo Varenicline in the evening)

Day 4-7: 0.5 mg BID

Day 8 to end of treatment: 1 mg BID

This group will remain on Varenicline 1 mg BID x 12 weeks post TQD.

1 week prior to the TQD: Placebo Bupropion will be added:

Day 1-3: 1 pill q AM

Day 4 to end of treatment: 1 pill BID

Placebo Bupropion will be continued for 12 weeks post TQD.

#### **Nicotine Patch Adaptive Treatment Arm (n=75)**

Participants who chose Nicotine Patch-based treatment and are then randomized to the Nicotine Patch Adaptive Treatment Arm will receive the following:

4 weeks prior to TQD: start on Nicotine Patch with the following dosing:

14 mg/day for participants smoking 5-10 cigarettes per day

21 mg/day for participants smoking 11-20 cigarettes per day

42 mg/day for participants smoking 20 or more cigarettes per day

This group will remain on this treatment for 4 weeks pre-TQD, then 12 weeks post TQD.

At the 2 week pre-TQD visit, this group will be assessed for “Response” to pre-quit Nicotine Patch:

**a. Nicotine Patch Non-Responders:** Participants who do NOT show > 50% reduction in cigarettes-per-day from baseline will be continued on Nicotine Patch, and Bupropion will be added as a “rescue medication”.

1 week prior to the TQD: Bupropion will be added to their regimen with this schedule:

Day 1-3: 150 mg q AM

Day 4 to end of treatment: 150 mg BID

Bupropion will be continued for 12 weeks post TQD.

**b. Nicotine Patch Responders:** Participants who show > 50% reduction in cigarettes-per-day from baseline will be continued on Nicotine Patch as their only active medication.

1 week prior to the TQD: Placebo Bupropion will be added

Day 1-3: 1 pill q AM

Day 4 to end of treatment: 1 pill BID

Placebo Bupropion will be continued for 12 weeks post TQD.

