#### 7.1.1. Dose Modification

Dosing of medications will follow FDA recommendations. If a participant experiences a side effect or symptom that may be ameliorated by dose adjustment (e.g. nausea while using the nicotine patch), the study physician or Physician Assistant will make these adjustments. The decisions to make the adjustments will be based on clinical judgment.

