### 7.2 Rationale for Selection of Dose, Regimen, and Treatment Duration

All dosing schedules used are based on FDA-approved dosing for these FDA-approved medications - but with minor modifications to fit study design requirements. For example:

**Varenicline:** Varenicline for control group is dosed exactly as normally prescribed but is continued for 12 weeks instead of 11 weeks post quit. In study group subjects, Varenicline is also used exactly as normally prescribed but is started 4 weeks prior to TQD instead of 1 week prior.

**Bupropion:** Bupropion is dosed exactly as is described for smoking cessation (started 1 week prior to quit day, continued for 12 weeks).

**Nicotine Patch:** Nicotine patch is dosed according to patient's use of nicotine – smokers who use 10 cpd or fewer will be on 14 mg patch, those who smoke 11-20 cpd will use a 21 mg patch and those who smoke over 20 cpd will be on a 42 mg patch. This parallels findings in our trial on adaptive treatments using nicotine patch in which participants were randomized to pre-quit nicotine patch of 21 mg vs. 42 mg with the finding that high use smokers showed higher abstinence (with allocation arms combined) using 42 mg Nicotine Patch, whereas low-use smokers showed higher abstinence (with allocation arms combined) using a 21 mg Nicotine Patch. In a follow-up study, participants were given a nicotine patch of 42 mg for CO >30 and 21 mg patch for CO ≤ 30. Post-hoc regression analysis showed that a CO level of 30 was most highly correlated with 23 cigs/day (Rose & Behm, 2013).

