## Appendix 4: Cost of Smoking

*These next questions are about the cost of cigarettes to you.*

1. How do you usually buy your cigarettes?
- 1 = By the Pack
  - 2 = By the Carton
  - 3 = Individually
  - 0 = Don't know

|                                                                                     |
|-------------------------------------------------------------------------------------|
| IF 1 = go to Question 43a
IF 2 = go to Question 43b
IF 3 = go to Question 43c |
|-------------------------------------------------------------------------------------|

- 1a. How much did you pay for the LAST PACK of cigarettes you bought?

\$ \_\_\_\_ . \_\_\_\_ \$1.00-\$10.00)

- 1b. How much did you pay for the LAST CARTON of cigarettes you bought?

\$ \_\_\_\_ . \_\_\_\_ (\$1.00 – \$99.00)

- 1c. How much did you pay for the LAST CIGARETTE you bought?

. \_\_\_\_ ¢ ( 0-99¢ )

|                                                                                                                                |
|--------------------------------------------------------------------------------------------------------------------------------|
| 44. Calculate: Cost of 1 cigarette: (Pack holds 20 cigs – so divide by 20) (Carton holds 200 so divide by 200) (do not report) |
|--------------------------------------------------------------------------------------------------------------------------------|

|                                                                                    |
|------------------------------------------------------------------------------------|
| 44a. Calculate Cigs per day x cost of each cig = Cost per day. Report Cost per day |
|------------------------------------------------------------------------------------|

|                                                                       |
|-----------------------------------------------------------------------|
| 44b. Calculate Cost per week = cost per day x 7. Report cost per week |
|-----------------------------------------------------------------------|

|                                                                          |
|--------------------------------------------------------------------------|
| 44c. Calculate Cost per month = cost per day x 30. Report cost per month |
|--------------------------------------------------------------------------|

|                                                                          |

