## **Appendix 14: Fagerström Test of Nicotine Dependence (FTND)(Heatherton, Kozlowski, Frecker, & Fagerstrom, 1991)**

1. How soon after you wake up do you smoke your first cigarette?  
3= Within 5 minutes  
2= 6-30 minutes  
1=31-60 minutes  
0= More than 60 min
2. Do you find it difficult to refrain from smoking in places where it is forbidden, (e.g. in church, at the library, in the cinema)?  
0 = No  
1 = Yes
3. Which cigarette would hate most to give up?  
1 = The first one in the morning  
0 = All others
4. How many cigarettes per day do you smoke?  
0= 10 or less  
1= 11-20  
2= 21-30  
3= 31 or more
5. Do you smoke more frequently during the first hours after waking than the rest of the day?  
0 = No  
1 = Yes
6. Do you smoke when you are so ill that you are in bed most of the day?  
0 = No  
1 = Yes

Calculate: Add scores of all 6 items.

1-2 = low dependence  
3-4 = low-moderate dependence  
5-7 = moderate dependence  
8+ = high dependence

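### In the adaptive patch arm, Section 10.2 gives a smoker of exactly 20 cigarettes per day two starting doses, 21 mg and 42 mg; Section 7.2 gives only 21 mg

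*Protocol*

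**What the plan says.** Section 10.2 sets the starting patch dose in the Nicotine Patch Adaptive arm by baseline cpd. The lowest band, 5 to 10 cpd, receives 14 mg. The next two lines read "21 mg/day for participants smoking 11-20 cigarettes per day" and "42 mg/day for participants smoking 20 or more cigarettes per day". The dose is then kept for the 4 weeks before the target quit day (TQD) and the 12 weeks after it.

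Section 7.2, which gives the rationale for dose, states the upper bands as "11-20 cpd will use a 21 mg patch and those who smoke over 20 cpd will be on a 42 mg patch". Its patch paragraph does not say which arm the bands apply to.

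The Nicotine Patch Standard arm in Section 10.2 has two bands only: 14 mg for 5 to 10 cpd, and 21 mg from 11 cpd upwards.

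**The concern.** Section 10.2 is the text from which study staff and the research pharmacy would take a dose, and at 20 cpd it gives two answers. Two participants with the same baseline consumption, both randomised to the adaptive patch arm, could start on 21 mg and 42 mg, and both would be treated according to the protocol as written.

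The value is one that can be expected to occur. The cost worksheet in Appendix 4 notes "Pack holds 20 cigs", so the boundary is one pack a day, and Section 9.1 admits anyone smoking 5 or more cpd with no upper limit.

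The dose also matters to the adaptive algorithm. Response is judged at the visit 2 weeks before the TQD, after 2 weeks on the starting dose. It decides whether active or placebo bupropion is added. An ambiguous starting dose therefore comes before the one decision that defines the adaptive strategy.

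**Working it through.** The plan states no figure to reproduce here. The check is whether each set of bands sends every cpd value to exactly one dose.

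**Inputs**
- Adaptive patch arm, Section 10.2: 14 mg if 5 ≤ cpd ≤ 10; 21 mg if 11 ≤ cpd ≤ 20; 42 mg if cpd ≥ 20.
- Dose rationale, Section 7.2: 14 mg if cpd ≤ 10; 21 mg if 11 ≤ cpd ≤ 20; 42 mg if cpd > 20.
- Standard patch arm, Section 10.2: 14 mg if 5 ≤ cpd ≤ 10; 21 mg if cpd ≥ 11.
- Eligibility, Section 9.1: cpd ≥ 5.

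**Result.** Each scheme was applied to every whole number from 5 to 60 cpd. The only value that does not receive exactly one dose is 20 cpd under the adaptive-arm schedule. Around the boundary:

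| cpd | 10.2, adaptive patch | 7.2 | 10.2, standard patch |
|---|---|---|---|
| 19 | 21 mg | 21 mg | 21 mg |
| 20 | 21 mg and 42 mg | 21 mg | 21 mg |
| 21 | 42 mg | 42 mg | 21 mg |

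**Size of the discrepancy.** 42/21 = 2, a twofold difference in daily dose.

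**Duration.** 4 weeks before the TQD + 12 weeks after = 16 weeks. Response is assessed 4 − 2 = 2 weeks after the patch is started.

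**After correction.** If the 42 mg band starts above 20 cpd, every whole number from 5 to 60 has one dose, and 20 cpd receives 21 mg.

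**A separate difference.** The last row of the table shows that above 20 cpd the unlabelled bands in Section 7.2 give 42 mg, while the standard-arm schedule gives 21 mg. This is not part of the overlap. It arises because Section 7.2 does not name an arm.

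**The case against.** The best reply is that the intended rule can be recovered. Section 7.2 gives a clean cut, the overlap is a single integer in one of four arms, and a careful reader who compares the two sections will settle on 21 mg. This stands as far as severity goes: the point is minor and the correction is not in doubt. It does not remove the error, because Section 7.2 is a rationale, Section 10.2 is the schedule, and nothing says which one prevails.

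Nor does clinical discretion fill the gap. Section 7.1.1 applies "If a participant experiences a side effect or symptom that may be ameliorated by dose adjustment", which concerns a later change of dose and not the starting dose.

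Some stronger readings are tempting, but the documents do not support them.

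- *That the cited evidence shows where the cut belongs.* Section 7.2 reports that in a follow-up study "participants were given a nicotine patch of 42 mg for CO >30 and 21 mg patch" at lower CO, and adds "Post-hoc regression analysis showed that a CO level of 30 was most highly correlated with 23 cigs/day". Since 23 − 20 = 3, 20 cpd lies below that point, but so do 21 and 22 cpd, which Section 7.2 itself places on 42 mg. A post-hoc correlation cannot choose between a cut at 20 and a cut just above it. The Appendix 14 item "How many cigarettes per day do you smoke" does keep 20 in the 11–20 category, but that is a questionnaire score and not a dosing rule. Only the explicit bands in Section 7.2 decide the matter.
- *That many participants are affected, because 20 cpd is one pack.* The pack size shows that the value can arise, not how often. The protocol gives no distribution of baseline cpd.
- *That 42 mg was meant for the adaptive arm only.* The varenicline paragraph of Section 7.2 separates control from study group, but the patch paragraph does not. Section 10.2 calls the control treatment standard of care, which is consistent with a 21 mg ceiling but does not state the reason for it. The documents leave this open.

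**Conclusion.** The inconsistency is real and minor. Section 10.2 is wrong as written at exactly 20 cpd in the adaptive patch arm: it contradicts itself, and it contradicts Section 7.2. The consequence is a twofold ambiguity in starting dose for an unknown number of the 75 participants planned for that arm.

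A reader might infer that the primary comparison is compromised. The documents do not support that. Assignment to adaptive or standard treatment, the definition of 30-day abstinence at 12 weeks and the stated power calculation do not use the cpd bands.

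The conclusion rests on the wording of the two sections and on treating cpd as a whole number. It needs no assumption about how many participants report 20 cpd, or about the clinical effect of the higher dose. Whether the 42 mg step was ever meant to reach the standard arm is a question for the sponsor and is not established as an error.

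**What to change.** In Section 10.2, adaptive patch arm, replace the lower limit of the 42 mg band with more than 20 cpd, so that it agrees with Section 7.2. Notify the research pharmacy and the dispensing staff of the corrected cut.

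Separately, ask the sponsor whether the 42 mg band in Section 7.2 applies to the standard arm. If it does not, align Section 7.2 with the standard-arm schedule by stating which arm the band belongs to. If it does, the standard-arm schedule in Section 10.2 is the text to amend.

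The first change is one phrase and a pharmacy notice. The second is one query and, if the answer is no, a short clarification in Section 7.2. Correcting the overlap adds no participants, visits or procedures.

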#### **Nicotine Patch Standard Treatment Arm (n=75)**

Participants who chose Nicotine Patch-based treatment and are then randomized to the Nicotine Patch Standard Treatment will receive the following:

4 weeks prior to TQD they will be started on placebo Nicotine Patch once per day.

On the TQD, placebo Nicotine Patch will be stopped and real Nicotine patch will be started with this dosing:

14 mg/day for participants smoking 5-10 cigarettes-per-day

21 mg/day for participants smoking 11 or more cigarettes-per-day

This group will remain on Nicotine Patch once per day x 12 weeks post TQD.

1 week prior to the TQD, Placebo Bupropion will be added:

Day 1-3: 1 pill q AM

Day 4 to end of treatment: 1 pill BID

Placebo Bupropion will be continued for 12 weeks post TQD

### 10.3 End of Treatment

At the end of treatment (12-week post-quit study visit) study staff will administer questionnaires (detailed further in section 10.7) and a program evaluation questionnaire. Participants will return all unused medications and empty pill bottles.

### 10.4 Follow-up Period

Following the End of Treatment, participants will receive two follow-up phone assessments (detailed further in section 10.7). These phone assessments will occur at 26-weeks post-TQD and 52-weeks post-TQD. If participants are not currently abstinent from tobacco at the End of Treatment, a referral to clinical resources within the TSCP will be offered.

**Follow up Study Assessment Visits:** At each assessment visit, there will be a standardized evaluation. The screening will be provided through the Duke Smoking Cessation Program for clinical purposes. Later assessments (Enrollment, Medication Response, 2- and 12-week post quit) will be provided by the CTA. During these visits there will be multiple self-report assessments (see below) as well as CO testing. Finally each participant will receive a total of 10 phone calls out to 1 year post quit attempt. Biochemically confirmed 30-day continuous abstinence at twelve weeks post-Target Quit Day is the primary endpoint to determine abstinence. Other endpoints, including biochemically confirmed 7-day point prevalent abstinence at two and twelve weeks post-TQD and self-reported abstinence rates via phone-based assessment up to 52-week post-TQD, will also assess abstinence as secondary measures.

**Phone-based Assessment Time Table:** The phone assessments function to collect data on study participants but also to check on difficulties with medications, medication side effects and to remind participants of upcoming visits. The timing is as follows:

|    |                                            |
|----|--------------------------------------------|
| 1  | 1 day after the Enrollment Visit           |
| 2  | 1 day before the Medication Response Visit |
| 3  | 1 day pre-TQD                              |
| 4  | 1 day post-TQD                             |
| 5  | 1-week post-TQD visit                      |
| 6  | 1 day before the 2-week post-TQD visit     |
| 7  | 6-week post-TQD time point                 |
| 8  | 1 day before the 12 week post-TQD visit    |
| 9  | 26 week post-TQD time point                |
| 10 | 52 week post-TQD time point                |

### 10.5 End of Study

Study participation will end with each participant after the 52-week post TQD phone assessment. If participants cannot be reached by phone, they will be contacted by additional means including email or other contact methods listed. If they are still not able to be contacted, they will be listed as "lost to follow up" for purposes of analysis of results (see management of missing data in analysis). If participants are not abstinent from tobacco at the End of Treatment, a referral to clinical resources within the TSCP will be offered. After all participants have completed the study, study data collection period will be considered over and the team will begin analysis of results. Analysis may continue for up to 5 years. This is necessary because of multiple sub-analyses that may be performed on the large quantity of data generated from this trial. After this 5-year period, it is expected that the trial will lock the data.

## **10.6 Early Withdrawal of Subject(s)**

### **10.6.1. Criteria for Early Withdrawal**

Subjects may voluntarily withdraw from the study at any time. The PI may also withdraw a subject from the study at any time based on his/her discretion. Reasons for PI-initiated withdrawal may include, but is not limited to the following:

- Adverse events
- Abnormal test procedure results
- Protocol deviation
- Administrative issues
- Disease progression
- Pregnancy

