### 7.4 Definition of Evaluable Subjects, On Study, and End of Study

Participants who enroll in the study will be “evaluable.” De-identified data from subjects who sign consent for screening will also be used for creation of the Consort Diagram – to show which individuals were excluded or did not sign consent vs. those who were enrolled. Data from subjects who withdraw from the study will still be considered evaluable.

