### **10.6.2. Follow-up Requirements for Early Withdrawal**

If a participant has cause for premature withdrawal, or if the PI decides that the participant should withdraw, he or she will be asked to attend a Premature Withdrawal Visit. If this occurs before the 12-week post quit visit (final treatment visit), the Premature Withdrawal Visit will essentially mirror the 12-week post quit visit (if the subject is able). If the premature Withdrawal occurs after the 12-week visit, then the patient will simply be called on the phone for a final phone call assessment then withdrawn with payment for the encounters he/she was able to complete.

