### 13.3 Handling of missing values, censoring, and discontinuations

An intent-to-treat approach will be taken in which any subjects lost to follow-up after the point of randomization will be counted as non-abstinent. In addition, a sensitivity analysis will be conducted to determine the impact of “missingness” and smoking at previously observed time-points.

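### Section 10.6 does not separate stopping study medication from leaving the study, so investigator withdrawal can create avoidable missing week-12 outcomes

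*Protocol*

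**What the plan says.** **Leaving the study.** Section 10.6.1 lets participants leave voluntarily and adds: "The PI may also withdraw a subject from the study at any time based on his/her discretion". The list of grounds is open-ended: "Reasons for PI-initiated withdrawal may include, but is not limited to the following". It names adverse events, abnormal test results, protocol deviation, administrative issues, disease progression and pregnancy. Section 10.6 has no category for a participant who is off medication but still followed.

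**What is collected afterwards.** For an exit before week 12, Section 10.6.2 asks for one visit: "the Premature Withdrawal Visit will essentially mirror the 12-week post quit visit", if the participant is able. For an exit after week 12, "then the patient will simply be called on the phone for a final phone call assessment then withdrawn". No further contact is specified in either case.

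**What the analysis needs.** Section 3.1 codes a participant abstinent only if self-report and CO both confirm it, at 12 weeks after the target quit day (TQD). Section 13.4 (Analysis of Primary Outcome) includes all enrolled participants under intent-to-treat. Section 13.3 (missing values) says that "any subjects lost to follow-up after the point of randomization will be counted as non-abstinent". Section 7.4 says: "Data from subjects who withdraw from the study will still be considered evaluable".

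**The concern.** Adverse events, protocol deviations and administrative problems may be reasons to stop a drug. They are not in themselves reasons to stop measuring smoking. As written, a participant withdrawn on such grounds who would still attend at week 12 is not asked to. The 12-week CO visit and the later calls already exist in the schedule, so the loss is avoidable. No analysis can restore outcomes that were never collected.

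The arms also differ in drug exposure. Under Section 10.2, adaptive participants receive active varenicline from 4 weeks before the TQD rather than 1 week (3 weeks more), or active patch from 4 weeks before rather than from the TQD (4 weeks more). Adaptive non-responders then receive active bupropion, while the standard arms receive placebo bupropion. If tolerability exits follow exposure, the missing outcomes would not be balanced between the arms.

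**Working it through.** **1. How would a participant withdrawn before week 12 be scored?** The protocol supports two readings.

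- *Non-abstinent.* Section 3.1 needs both self-report and CO at week 12, and this participant has neither at that time. Section 13.3 (missing values) scores those lost to follow-up as non-abstinent. This is the more natural reading. However, Section 10.5 uses the term lost to follow-up for people who cannot be contacted, which does not clearly cover someone the investigator withdrew.
- *Scored on the early visit.* Section 7.4 keeps withdrawn participants' data evaluable, and the early visit repeats the 12-week assessments. A withdrawal later than 30 days after the TQD (about 30/7 = 4.3 weeks) could yield a 30-day abstinence report with a confirming CO. Entered as the 12-week result, it would count as a success whatever happened later.

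The two readings err in opposite directions for anyone abstinent at the early visit. Neither gives the week-12 outcome.

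**2. Reproduce the planned figures.** The inputs, from Section 13.4 (Sample Size Calculation), are 39.7% adaptive and 23.4% standard, 150 per arm, two-sided alpha 0.05. The stated results are 248 participants for 80% power and 87% power at 300.

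- Variance sum: 0.397 × 0.603 + 0.234 × 0.766 = 0.4186. Difference: 0.163.
- Unpooled, no continuity correction: n per arm = (1.960 + 0.842)² × 0.4186 / 0.163² = 123.7, so 124 per arm and 248 in total. Power at 150 per arm is 87.0%. Both stated figures match.
- Pooled variance under the null, no correction: 254 in total, and 86.3% power at 300. This version is used below.

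As a separate matter, the protocol says a continuity correction was applied. With one, the figures would be 278 and about 83.4%.

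**3. Effect of scoring withdrawn participants as smokers.** Let w be the share of an arm withdrawn before week 12 beyond what the planned rates already contain. Let r be those participants' true week-12 abstinence as a fraction of their arm's planned rate. Then:

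observed rate = planned rate × (1 − w × r)

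The protocol gives neither w nor r by arm, so both are assumptions shown over a range.

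| Excess withdrawal | r = 0.25 | r = 0.5 | r = 1.0 |
|---|---|---|---|
| None | 16.3 points, 86.3% | 16.3 points, 86.3% | 16.3 points, 86.3% |
| 5%, adaptive only | 15.8 points, 84.3% | 15.3 points, 82.1% | 14.3 points, 77.0% |
| 10%, adaptive only | 15.3 points, 82.1% | 14.3 points, 77.0% | 12.3 points, 64.9% |
| 10%, both arms | 15.9 points, 85.0% | 15.5 points, 83.7% | 14.7 points, 80.8% |

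Each cell shows the difference between arms, then power at 150 per arm. Example: with w = 10% and r = 1 in the adaptive arm only, the adaptive rate is 0.397 × 0.90 = 0.357 and the difference is 0.357 − 0.234 = 0.123.

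**The case against.** **Withdrawal is permitted, not required.** This stands. Section 7.1.1 allows dose adjustment for side effects during the study. The phone form in Appendix 19 asks whether medication was stopped, and Appendix 11 records days of use and reasons for non-use. The protocol therefore expects some participants to be off drug and still followed. A reader might infer that anyone who stops a drug is removed and counted as a smoker, but the documents do not say that. What remains is that Section 10.6 does not protect the follow-up of those the investigator does withdraw.

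**Attrition is already in the assumed rates.** Section 10.6.3 says so, and only withdrawal beyond that level affects the table. The point is not fully met, because the planned 38.2% for adaptive varenicline comes from pre-quit varenicline without adaptation and so cannot include bupropion-related exits.

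**Multiple imputation is planned as a sensitivity analysis.** It tests the non-abstinent assumption, but it has no observed outcomes after withdrawal to draw on.

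**The mapping of early visits to endpoint windows is often left to a statistical analysis plan.** This is fair, so the open scoring question is secondary. An analysis plan could settle the scoring but could not supply the week-12 data.

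**The bias is conservative.** If withdrawn participants are scored as smokers and the excess is in the adaptive arm, the effect shrinks. This stands and limits the severity.

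**Conclusion.** The point holds as a gap in follow-up that should be fixed; it does not invalidate the design. Section 10.6 allows investigator withdrawal on grounds that need not end follow-up, and then specifies no outcome collection beyond one visit or call. Exits before week 12 affect the primary outcome. Exits after it affect only the 26- and 52-week calls.

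The size is illustrative. A 5 to 10% excess in the adaptive arm reduces the 16.3-point difference to between 15.8 and 12.3 points, and power from about 86% to between 84% and 65%. This assumes that withdrawn participants are scored as smokers, that the standard arm has no such excess, and that r lies between 0.25 and 1.

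Three stronger readings are not supported:

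- *That exits will be more frequent in the adaptive arm.* The exposure difference makes this plausible, but no withdrawal rate by arm is given.
- *That the bupropion discontinuation figures in Section 5.2 fix the loss.* The 7–12% there refers to people reporting adverse effects, not to everyone given bupropion. Using it would also require every stopper to be withdrawn from the study.
- *That discretion lets an investigator improve results by removing visible smokers.* Under intent-to-treat, a removed smoker scored non-abstinent stays in the denominator, so the result is unchanged.

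**What to change.** In Section 10.6.1, distinguish stopping study medication from withdrawing consent to follow-up. Leave the clinical grounds for stopping medication as they are, and state that only withdrawal of consent to follow-up ends data collection.

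In Section 10.6.2, keep everyone else on the existing schedule: the remaining calls, the 12-week CO visit, and the 26- and 52-week calls. State that Premature Withdrawal Visit data are not used as the 12-week endpoint.

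The cost is an amendment to the protocol and consent wording. The visits and calls are already scheduled. The downside is continued contact with some participants who are off drug.
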